### Primary endpoint, secondary endpoints/data collection

The primary endpoint is the HMO composition (3-fucosyllactose, 3’-sialyllactose) in human breast milk after supplementation prenatally. Secondary endpoints are clinical and safety outcomes of mothers (infections, alterations in vaginal microbiome) and infants (preterm birth, sepsis, growth, gastrointestinal complications) and the effects on the microbiome composition in the rectovaginal tract of mothers at delivery and in the gut of term and preterm infants.

### Sample collection

After informed consent the participants take one capsule of probiotics once daily until delivery. At the timepoint of inclusion, samples to describe the “baseline microbiome” will be collected in the form of a rectovaginal swab and a stool sample. As soon as labor begins or imminent delivery is likely, a rectovaginal swab and stool sample are taken by a midwife or obstetrician to test hypothesis 2 (increased abundance of *Lactobacillus* and *Bifidobacteria* in women’s vaginal flora due to probiotics supplementation in pregnancy). After birth samples of colostrum, breast milk and neonatal stool are gathered on day one, two, three, seven, fourteen and 28, stored and frozen at -80 °C. Depending on gestational age, stage of enteral feeding, and growth, preterm infants are fed exclusively breastmilk, donor milk, formula milk or a mixture. This will be considered in the final analysis. Additional samples (a stool sample of the infant and a breast milk sample from the mother when still breastfeeding) will be collected at the follow-up visit at three-month, 1 year and 5 years of age by study personnel. A standardized questionnaire about former parents’ history, infections, allergies, postpartum course, provided by the families in the first week, completed by case report forms at day 3, day 28 and at three months, one year and five-year follow-up (see Fig. 2).

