Probiotics are widely used in preterm infants as a NEC prophylaxis [51, 52] and were supplemented to pregnant women within clinical trials [1]. To identify the scientific value of this study, we performed a literature review on probiotic supplementation during pregnancy reporting on various maternal and neonatal outcome parameters. Interestingly, RCTs using *Lactobacillus acidophilus* and *Bifidobacterium animals subsp. lactis and B. infantis* probiotics not only showed a significant impact on maternal outcomes such as decreased rates of GDM [31] or reduced colonization rates with group B Streptococcus [37], but as well demonstrated significant measurable effects on neonatal characteristics such as microbiome composition, immune phenotype (cytokine secretion) and rates of atopic symptoms [40, 41]. In conclusion, however, study results are largely inconclusive across the studies performed, which might mainly be due to differences of in- and exclusion criteria, dosage of probiotic supplements and most importantly, targeted outcomes. To our best knowledge and as a result of our literature review, only one study has investigated HMO composition of human breast milk after probiotic supplementation of pregnant women. While demonstrating promising results by showing increased levels of several breast milk HMOs after birth, the study was limited to included pregnancies of > 36 weeks and infants born at term. Hence, the effects of probiotic supplementation have so far never been studied in the context of HMO breast milk composition at preterm birth. Our main hypothesis is that supplementation of *Lactobacillus acidophilus* and *Bifidobacterium animals subsp. lactis and Bifidobacterium infantis* during pregnancy will increase the abundance of HMOs at the time of preterm delivery. Based on the findings of Seppo et al. [1], we propose changes of the concentration of 3’-fucosyllactose and 3’-sialyllactose in women supplemented with probiotics when compared to non-treated controls. Our second hypothesis of vaginal microbiome signatures that are associated with probiotic intake are based on study results showing a reduction in vaginal dysbiosis and increased amounts of favorable bacteria [35, 39, 59]. As a secondary outcome we will explore signatures of the neonatal microbiome of supplemented mothers as compared with non-supplemented controls. Previous observational studies and RCTs indicate that probiotics are safe and well tolerated in an adequate clinical setting. Results of this study may have implications for the management of pregnancies at risk for preterm delivery. A stable neonatal microbiome and dysbiosis prevention may improve short and long-term outcomes of preterm infants. If this study confirms our hypotheses, placebo-controlled randomized trials will be necessary to verify the results.

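### Hypothesis 2 is about the vaginal flora but is tested on a combined rectovaginal swab, so a rise under the swallowed probiotic cannot be assigned to the vagina

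*Protocol article*

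**What the plan says.** The Background of the protocol article lists, as a further hypothesis, that supplementation increases Lactobacillus and Bifidobacteria in the vaginal flora. Sample collection numbers this hypothesis 2 and describes it as an increase "in women’s vaginal flora due to probiotics supplementation in pregnancy". For its test, at labour or imminent delivery, "a rectovaginal swab and stool sample are taken by a midwife or obstetrician to test hypothesis 2". At inclusion, "samples to describe the “baseline microbiome” will be collected in the form of a rectovaginal swab and a stool sample". So the same two specimen types exist at both time points. No separate vaginal swab is mentioned anywhere.

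The section on primary and secondary endpoints carries two wordings for the maternal microbiome. One is "clinical and safety outcomes of mothers (infections, alterations in vaginal microbiome"; the other is "the effects on the microbiome composition in the rectovaginal tract of mothers at delivery". It does not say how the one swab provides both.

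The Conclusion keeps the vaginal wording. It states an aim of defining signatures of the vaginal flora and refers to "Our second hypothesis of vaginal microbiome signatures that are associated with probiotic intake".

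**The concern.** The hypothesis names one body site, and the specimen samples two. That would matter little if the treatment could not act on the second site, but here it can. The intervention is a daily capsule containing Bifidobacterium and Lactobacillus strains (Probiotic formula), and the control arm takes none (Intervention/Control). The mechanism set out with Figure 1 begins with more of these genera after maternal intake and has bacteria moving out from the gut. The trial therefore expects an intestinal increase in the very genera that hypothesis 2 counts.

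If the swab shows more of them in the probiotic arm, the plan as worded invites the conclusion that the vaginal flora changed. The data could equally reflect rectal carriage. The Conclusion foresees possible implications for managing pregnancies at risk of preterm delivery, so a claim about the wrong site would not be harmless.

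**Working it through.** The documents give no figure on this point, so there is nothing to reproduce. The check sets the statements side by side and then asks, with assumed inputs, whether the artefact can arise.

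**Step 1: site by section of the protocol article**

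| Section | Site named | Target |
|---|---|---|
| Background (list of hypotheses) | vaginal | Lactobacillus, Bifidobacteria |
| Sample collection (hypothesis 2) | vaginal | Lactobacillus, Bifidobacteria |
| Sample collection (specimen) | rectovaginal swab, plus stool | – |
| Endpoints, maternal outcomes | vaginal | microbiome alterations |
| Endpoints, microbiome effects | rectovaginal | composition at delivery |
| Conclusion | vaginal | signatures, no genus named |

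The specimen matches only one of the five statements of hypothesis, endpoint or aim.

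**Step 2: can the analysis recover the site?** A laboratory assay of the swab identifies organisms, not the site they came from. Randomisation balances rectal carriage before treatment, but carriage after treatment may differ by arm because of the treatment. An analysis plan cannot extract a vaginal measurement from a mixed specimen without knowing the rectal share.

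**Step 3: illustration (all inputs assumed, none from the documents).** Let *f* be the rectal share of the swab's DNA, the same in both arms; *v* the vaginal abundance of a genus, also the same in both arms; and *r0*, *r1* its rectal abundance without and with probiotic. Then

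swab abundance = (1 − f)·v + f·r

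apparent ratio = [(1 − f)·v + f·r1] / [(1 − f)·v + f·r0]

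The assumed grid is v = 0.1%, 0.5% or 2%, and rectal abundance rising from 1% to 2%, 2% to 4% or 2% to 6%.

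- Lowest case at f = 5%, v = 2%, 1% to 2%: (1.90 + 0.10) / (1.90 + 0.05) = 2.00 / 1.95 = 1.03.
- Middle case at f = 10%, v = 0.5%, 2% to 4%: (0.45 + 0.40) / (0.45 + 0.20) = 0.85 / 0.65 = 1.31.
- Highest case at f = 50%, v = 0.1%, 2% to 6%: (0.05 + 3.00) / (0.05 + 1.00) = 3.05 / 1.05 = 2.90.

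| Rectal share f | Apparent ratio over the grid, no vaginal effect |
|---|---|
| 0 | 1.00 |
| 5% | 1.03 to 2.03 |
| 10% | 1.05 to 2.38 |
| 25% | 1.14 to 2.74 |
| 50% | 1.33 to 2.90 |

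Only a swab with no rectal material is free of the effect. The ratio approaches 1 when the genus is already abundant in the vagina relative to the rectal contribution, so the artefact may be large for one genus and negligible for another. The table shows that the artefact is possible and which way it points; it does not estimate its size in this trial.

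**The case against.** Several points on the other side are sound.

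- **Stool is collected.** The sentence that names the swab also names a stool sample, and both are taken at inclusion too. Intestinal carriage need not go unnoticed. This stands, and the fix relies on it. But stool can only show whether an intestinal rise occurred; it cannot isolate the vaginal part of the swab, and the article states no such use for it.
- **The size is undetermined.** This stands. Every abundance and share above is assumed, and it would be wrong to say that rectal carriage will produce a positive swab result. The documents support only that it could.
- **The endpoint section does not flatly oppose the hypothesis.** It contains both wordings, so it is mixed. Both need attention.
- **The Conclusion is less specific.** It speaks of vaginal signatures, not of the two genera, and it draws nothing from data. Only the Background and Sample collection carry the genus-level vaginal hypothesis.
- **The matter is secondary.** The primary endpoint and the sample size rest on milk oligosaccharides and are untouched. The Conclusion also says that placebo-controlled trials would be needed to verify the results. A placebo would not, however, resolve the site of a mixed swab.

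A reader might also infer that the inclusion swab will be used for description alone and left out of the comparison, at a loss of precision. The text does not support that. It gives description as a purpose, without saying that it is the only one, and the Statistical analysis section leaves details to a separate plan, where baseline adjustment commonly belongs. Adjustment would not cure the site problem in any case, because the inclusion swab is equally mixed.

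**Conclusion.** The concern holds for the match between hypothesis and specimen. As described, the trial can test whether the probiotic changes Lactobacillus and Bifidobacteria in a rectovaginal swab; it cannot attribute such a change to the vagina. The likely error is directional: an intestinal increase in the probiotic arm would look like support for hypothesis 2. Its size cannot be given, because the documents state neither the abundances nor the rectal share of the swab.

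This rests on two premises from the article: that the swab combines rectal and vaginal material, as its name says, and that the swallowed product contains the measured genera. It also requires that intake can alter rectal carriage, which the article's own mechanism makes plausible but does not establish. The point is more than a matter of wording, since it changes what the trial may conclude, but it is confined to a secondary hypothesis.

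**What to change.** 1. Restate hypothesis 2 as an increase in the rectovaginal flora, in the Background and in Sample collection.
2. In the endpoint section, use *rectovaginal* for both maternal microbiome wordings. Changing hypothesis 2 alone would leave the vaginal wording there unrepaired.
3. Align the vaginal-signature statements in the Conclusion in the same way.
4. State that no vagina-specific claim will be made from this swab.
5. Name the stool samples from inclusion and delivery as a supportive check on whether any increase in the swab mirrors an intestinal one, and say that stool cannot isolate the vaginal contribution.

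No new sample or visit is needed. The cost is a narrower secondary claim and a short stool comparison. The statistical analysis plan may still be finalised until shortly before the last inclusion, so the last two items can be placed there.

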### Data collection

Standardized Case Report Forms (CRFs) are used to record information from the mother prenatally and postnatally from mother and infant. At the time of inclusion (CRF inclusion), closely after birth (CRF day 3), one month after birth (CRF day 28), at three months CRF 3 m (mother + infant), one- and five-year follow- up (CRF 12 and 60 m) (see Fig. 2).

Data collected at the follow-ups will be used to measure long-term outcomes (allergies, incidence of infections, re-admissions to the hospital). The CRFs are filled in manually by the study team (neonatologist, doctoral student and study nurse). Additionally, the women will be asked to keep a diary handed out at inclusion to document regularity of probiotic intake, infections, antibiotic therapy, allergies and possible side effects during the intake of probiotics. The inclusion-CRF collects information of former participant’s medical history e.g. preexistent diseases, the course of pregnancy, former pregnancies and allergies. The follow up CRFs collect data from both, mothers and infants. CRF day 3 includes information about the delivery mode, reason for delivery, infections and risk factors for microbiome dysbiosis. In CRF day 28 information about complications in puerperium, growth parameters and feeding of the infant is collected. This data will be collected via telephone interview. In case of birth before completed 32 weeks follow-up examination will take place onsite. At follow-up information on both, mother and infant will be recorded via CRFs.

**Fig. 2 Fig2:**
[figure not shown]
Flow chart of used CRFs

### HMO-assessment

Analysis of HMOs amount and composition will be performed at the Institute of Chemistry and Metabolomics of the University of Lübeck, Germany, by nuclear magnetic resonance (NMR) spectroscopy). To this end, samples of breast milk will be analyzed according to published protocols [54]. Briefly, proteins and lipids will be removed by ultrafiltration and after buffer addition to the filtrate, NMR spectra will be acquired. NMR spectra will be analyzed and compared with published data [54, 55] to (i) determine the secretor status of the woman and if the woman is Lewis positive or negative and to (ii) investigate if the concentration of HMOs in breast milk change with probiotic supplementation.

### Microbiome sequencing

To address hypothesis 3 (increased abundance of several bacteria in neonatal microbiome) 16s rRNA microbiome analyses will be performed at the Clinic for Infectiology and Microbiology at the University of Lübeck, Germany [53, 56]. To amplify partial sequences of 16 S rRNA gene linker and indices-containing primers targeting V3/V4 hypervariable regions of 16 S rRNA [29] will be used. Polymerase chain reaction will be performed starting with 98 °C for 30 s, followed with 30 cycles with 98 °C for 9 s, 55 °C for 60 s and 72 °C for 90 s finishing with 72 °C for ten minutes. Storage of amplicons at -20 °C until further processing is planned. Agarose gel electrophoresis will be used to estimate the amplicons concentrations. GeneRuler 100 bp DNA Ladder (Thermo Fischer Scientific, Waltham, USA) will be used as reference. Sequencing will be performed using MiSeq^®^ platform (Illumina^®^, San Diego, California, USA) and MiSeq^®^ reagent Kit V3 for 600 cycles. PhiX library will be set as positive control. To ensure absence of reagents contamination negative extraction controls will be integrated, too.

### Estimated sample size and power calculations

Based on the publication of Seppo et al. [1] who supplemented probiotics in pregnancies > 36th weeks calculations of sample sizes were performed.

**Table 2 Tab2:** Calculation minimal sample size based on data from Seppo et al. 2019 [1]

Human milk oligosaccharids	Supplementation	No supplementation	Minimal sample size
	mean [SD]	mean [SD]	*n*
3-fucosyllactose (µmol/mL)	413 [164]	312 [232]	73
3´-sialyllactose (µmol/mL)	833 [679]	516 [378]	55
difucosyllacto-*N*-hexaose (µmol/mL)	62.0 [43.3]	93.7 [47.7]	38
lacto-*N*-tetraose (µmol/mL)	509 [339]	861 [563]	32
lacto-*N*-fucopentaose I (µmol/mL)	2000 [585]	2450 [836]	47
6´-sialyllactose (µmol/mL)	472 [159]	567 [179]	58

*Legend SD* standard deviation; *n* estimated sample size

Table 2. lists HMO measurement means and standard deviations taken from Seppo et al. [1] for six different HMO subgroups. Column titled “n” lists minimal sample size numbers inferred via balanced Mann-Whitney U test. Calculations were performed with the R package ’pwrss’ [Bulus, M. (2023). pwrss: Statistical Power and Sample Size Calculation Tools. R package version 0.3.1.]. The significance threshold (acceptable type I error rate) was set to alpha = 0.05 and predictive power (acceptable Type II error rate) was set to 0.8. Dropout rate was considered to be 10%. Whereas sample size numbers in Seppo et al. [1] are unbalanced between treatment group and control group (50 vs. 31), we assumed balanced conditions in our analysis to minimize the total number of required samples. Based on these calculations we include 73 women taking the probiotics ( ≙ verum group) during pregnancy and 73 women without treatment ( ≙ control group). We choose the maximal calculated number n (Table 2.) as minimal sample size and add a 25% risk of drop out.

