### Intervention/Control

Study participants are randomly assigned to receive the probiotic mixture (intervention group *n* = 73) or not (control group *n* = 73). The intervention is one capsule of Bactiol^®^ Infantis per day until delivery. The proposed number of participants is calculated based on former studies (see below). A randomization sequence was created in advance to assign mother – infant pairs to a study arm. This trial is not blinded. The women and participating doctors know whether they are in the intervention or control group, and we are not using a placebo.

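### The announced 25% drop-out allowance is not in the 73 women per arm, which contain only 10%; at 25% loss, power for 3-fucosyllactose is about 72%, not 80%

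*Protocol article*

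**What the plan says.** All of the sizing is in the protocol article under 'Estimated sample size and power calculations'.

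- Table 2 lists means, SDs and a minimal n for six oligosaccharides from the earlier term-pregnancy study. The n values are described as "minimal sample size numbers inferred via balanced Mann-Whitney U test". The largest is 73, for 3-fucosyllactose.
- Design values: "The significance threshold (acceptable type I error rate) was set to alpha = 0.05" and "predictive power (acceptable Type II error rate) was set to 0.8". The second label mixes up power and type II error; the 0.8 works as power.
- First drop-out statement: "Dropout rate was considered to be 10" per cent.
- Enrolment: "Based on these calculations we include 73 women taking the probiotics", with 73 controls.
- Second drop-out statement: "We choose the maximal calculated number n (Table 2.) as minimal sample size and add a 25% risk of drop out".

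The section 'Intervention/Control' also gives 73 per arm. 'Screening and study participants' gives a total of approximately 130 women.

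**The concern.** One paragraph carries two drop-out rates. The second is said to be added to the largest Table 2 value, yet the number enrolled equals that value. Either the 25% was never applied, or 73 already contains it and the sentence is misplaced. Table 2 gives enough detail to tell which.

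This matters because 3-fucosyllactose is one of the two oligosaccharides named as the primary endpoint and the one that fixes the sample size. If loss reaches the protocol's own higher rate, the trial lacks the 80% power it states, and a null result would be read as more informative than it is. The protocol itself describes ways to lose women: withdrawal at their own request, and exclusion for delivery at another hospital or for irregular intake ('Stopping rules').

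**Working it through.** **Inputs from the protocol.** Means and SDs from Table 2; alpha 0.05; power 0.80; Mann-Whitney test; 1:1 allocation; drop-out 10% and 25%; 73 enrolled per arm.

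**Assumptions.** Two-sided test and normally distributed data, as neither is stated. The two-sided reading is supported by the table: a one-sided test with 10% drop-out gives about 58 for 3-fucosyllactose, not 73.

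**Step 1: reproduce Table 2.**

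- d = difference / √((SD₁² + SD₀²)/2)
- evaluable n per arm = 2 × (1.960 + 0.8416)² / d² × π/3, where π/3 is the Mann-Whitney efficiency factor for normal data
- enrolled n per arm = evaluable n / 0.90

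For 3-fucosyllactose:

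- SD = √((164² + 232²)/2) = 200.9
- d = (413 − 312)/200.9 = 0.503
- t-test n = 62.11; × π/3 = 65.04 evaluable
- 65.04/0.90 = 72.27, rounded up to 73

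| Oligosaccharide | d | Evaluable n | n/0.90 | Table 2 |
|---|---|---|---|---|
| 3-fucosyllactose | 0.503 | 65.04 | 72.27 | 73 |
| 3'-sialyllactose | 0.577 | 49.40 | 54.89 | 55 |
| difucosyllacto-N-hexaose | 0.696 | 33.95 | 37.72 | 38 |
| lacto-N-tetraose | 0.757 | 28.65 | 31.83 | 32 |
| lacto-N-fucopentaose I | 0.624 | 42.26 | 46.95 | 47 |
| 6'-sialyllactose | 0.561 | 52.20 | 58.01 | 58 |

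Five rows match after rounding up. The sixth differs only in how 58.01 is rounded.

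**Step 2: test the other readings of 73.**

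- No drop-out allowance: 65.04, rounded up to 66.
- 25% allowance: 65.04 × 1.25 = 81.3 (82), or 65.04/0.75 = 86.7 (87).

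Neither gives 73. The table values contain a 10% allowance and no 25% allowance.

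**Step 3: power with 73 enrolled per arm.** The evaluable number is multiplied by 3/π to give the equivalent t-test size m, and power is computed for d√(m/2).

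| Loss | Evaluable per arm | 3-fucosyllactose: t-based (normal approx.) | 3'-sialyllactose: t-based (normal approx.) |
|---|---|---|---|
| 10% | 73 × 0.90 = 65.7 | 0.798 (0.804) | 0.894 (0.898) |
| 25% | 73 × 0.75 = 54.75 | 0.721 (0.729) | 0.832 (0.839) |

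For 3-fucosyllactose at 25% loss: m = 54.75 × 3/π = 52.28, and 0.503 × √(52.28/2) = 2.57. A simulation of the Mann-Whitney test on normal data (20,000 runs) gave power of 0.709 with 54 per arm and 0.719 with 55.

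**Step 4: what a 25% allowance would require.**

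- Applied once to the uninflated number: 65.04/0.75 = 86.7, so 87 per arm; starting from the rounded 66, 66/0.75 = 88. Total 174 to 176.
- Taken literally, on top of 73: 73 × 1.25 = 91.25 (92) or 73/0.75 = 97.3 (98). This counts drop-out twice.

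**Step 5: the other enrolment figure.** Approximately 130 women is 65 per arm, about the uninflated requirement, against 146 for 73 per arm. At 25% loss, 65 × 0.75 = 48.75 per arm remain, and power for 3-fucosyllactose is about 67% (0.670 t-based, 0.679 normal approximation).

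**The case against.** The main objection is that the power loss is conditional. At the protocol's other rate, 10%, 73 enrolled women leave about 66 evaluable and power is 80%. Even at 25% loss, 3'-sialyllactose keeps more than 80%. The document does not say which rate is expected, nor what kinds of loss make up the 25%. This stands, so the 72% must be quoted as the power at 25% loss.

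It can also be said that the 10% inside Table 2 is inferred, since neither the inflation formula, the sidedness nor the distribution is given, and one row reproduces only up to rounding. That is true, but the pattern over six rows is hard to explain otherwise, and neither no allowance nor a 25% allowance gives 73. Whether the 10% was applied by dividing by 0.90 or multiplying by 1.1 cannot be settled and does not affect the conclusion.

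A third reading takes 73 as a minimum number of evaluable women, with recruitment to exceed it. The text does not support this: two sections give 73 per arm as the numbers included or assigned, and the only other total in the article is lower.

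Finally, nothing here biases the treatment estimate or raises the type I error. That is correct and limits the consequence to power, but the sample size statement is still wrong as written.

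**Conclusion.** The concern holds. The protocol announces a 25% drop-out allowance that its enrolled number does not contain; the 73 per arm carries 10%. With 25% loss, about 55 per arm are evaluable. Power for 3-fucosyllactose is then about 72% (71% to 73% across the methods used), a shortfall of 7 to 9 percentage points; for 3'-sialyllactose it is 83% to 84%. With 10% loss the stated 80% is met. These figures assume a two-sided test, normally distributed data and the effect sizes and SDs of Table 2. The contradiction between the two rates and the enrolled number depends on none of these assumptions.

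**What to change.** Keep 73 per arm and correct the text. State that the Table 2 values already include 10% drop-out, so that 73 enrolled gives about 66 evaluable women per arm and 80% power for 3-fucosyllactose. Then take one of two courses:

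1. If 10% is the expected loss, give the reason and delete the 25% sentence.
2. If 25% is plausible, say that about 55 per arm would be evaluable, with power of about 72% for 3-fucosyllactose and 83% for 3'-sialyllactose.

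Deleting the sentence while still expecting 25% would only hide the shortfall. If 25% is expected and 80% power is to be kept, apply that rate once to the uninflated 65 to 66 per arm, giving 87 to 88 per arm, rather than inflating 73 again.

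In the same edit, bring the approximately 130 women under 'Screening and study participants' into line with the total chosen, and label 0.8 as power.

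Restating the power is a wording change and needs no extra participants; the stated power becomes less favourable if 25% is acknowledged. Holding 80% at 25% loss would add 28 to 30 women to the planned 146 (174 to 176 in total).
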